## Abstract

**Introduction:**

Advances in modern medicine have led to people living longer and healthier
lives. Frailty is an emerging concept in medicine yet to be explored as a
risk factor in cardiac surgery. When it comes to CABG surgery, randomized
controlled clinical trials have primarily focused on low-risk (ROOBY,
CORONARY), elevated-risk (GOPCABE) or high-risk patients (BBS), but not on
frail patients. Therefore, we believe that off-pump CABG could be an
important technique in patients with limited functional capacity to respond
to surgical stress. In this study, the authors introduce the new national,
multicenter, randomized, controlled trial "FRAGILE", to be developed in the
main cardiac surgery centers of Brazil, to clarify the potential benefit of
off-pump CABG in frail patients.

**Methods:**

FRAGILE is a two-arm, parallel-group, multicentre, individually randomized
(1:1) controlled trial which will enroll 630 patients with blinded outcome
assessment (at 30 days, 6 months, 1 year, 2 years and 3 years), which aims
to compare adverse cardiac and cerebrovascular events after off-pump
*versus* on-pump CABG in pre-frail and frail patients.
Primary outcomes will be all-cause mortality, acute myocardial infarction,
cardiac arrest with successful resuscitation, low cardiac output
syndrome/cardiogenic shock, stroke, and coronary reintervention. Secondary
outcomes will be major adverse cardiac and cerebrovascular events, operative
time, mechanical ventilation time, hyperdynamic shock, new onset of atrial
fibrillation, renal replacement therapy, reoperation for bleeding,
pneumonia, length of stay in intensive care unit, length of stay in
hospital, number of units of blood transfused, graft patency, rate of
complete revascularization, neurobehavioral outcomes after cardiac surgery,
quality of life after cardiac surgery and costs.

**Discussion:**

FRAGILE trial will determine whether off-pump CABG is superior to
conventional on-pump CABG in the surgical treatment of pre-frail and frail
patients.

**Trial registration:**

ClinicalTrials.gov, ID: NCT02338947. Registered on August 29^th^
2014; last updated on March 21^st^ 2016.

**Table t1:** 

Abbreviations, acronyms & symbols				
ARDS	= Acute respiratory distress syndrome		OR	= Odds ratio
BBS	= Best bypass surgery		PCI	= Percutaneous coronary intervention
CABG	= Coronary artery bypass grafting		PROM	= Predicted risk of mortality or major morbidity
CI	= Confidence interval		RCTs	= Randomized controlled trials
CORONARY	= CABG Off- or On-Pump Revascularization Study		ROOBY	= Randomized on/off bypass
HR	= Hazards ratio		STS	= Society of Thoracic Surgeons

## INTRODUCTION

One of the most controversial areas of cardiac surgery has been whether off-pump
coronary artery bypass grafting (OPCAB) surgery is superior to conventional on-pump
coronary artery bypass grafting (CABG) surgery. There is an ongoing debate about the
benefits and disadvantages of OPCAB. Initial trials have shown that off-pump CABG is
feasible in selected low-risk patients and offers results similar to those of CABG
performed with the conventional on-pump technique (on-pump CABG)^[1,2]^. In institutions with experience in off-pump CABG, the rates of
major adverse events and of complete revascularization and graft patency have been
similar to those with on-pump CABG^[3]^. These positive results have been called into question by
reports of inferior graft patency and higher rates of repeat target-vessel
revascularization associated with off-pump CABG^[4,5]^.

The Randomized On/Off Bypass (ROOBY) trial^[6]^ showed that, among low-risk patients, the rate of death or
major adverse events at 30 days after surgery was similar with off-pump and on-pump
CABG, but off-pump CABG was associated with a higher rate of incomplete
revascularization at 1 year.

Short-term mortality and morbidity after off-pump and on-pump CABG were similar in a
recent trial involving 4752 patients with a mixed operative-risk profile (the CABG
Off- or On-Pump Revascularization Study [CORONARY])^[7]^.

The German Off-Pump Coronary Artery Bypass Grafting in Elderly Patients
(GOPCABE)^[8]^ study focused
exclusively on patients 75 years of age or older. However, this trial would not
elucidate the potential benefit of off-pump CABG in high-risk patients because this
specific group of German patients were moderate risk patients.

The results of the Best Bypass Surgery (BBS) trial^[9]^, performed on 341 high-risk patients (European
System for Cardiac Operative Risk Evaluation "EuroSCORE">5) undergoing on-pump
CABG or off-pump CABG, reported no significant differences in the composite of
adverse cardiac and cerebrovascular events or in any of the following outcomes:
all-cause mortality, acute myocardial infarction, cardiac arrest, low cardiac
output/cardiogenic shock, stroke, and coronary reintervention.

However, in our opinion, the definition of high-risk patient should be interpreted
carefully, since the EuroSCORE identifies patients based on 18 independent
variables, many of which were not considered in the study. Risk factors such as
previous cardiac surgery, critical preoperative state, emergency operation, and poor
left ventricular dysfunction were excluded. Furthermore, active endocarditis,
pulmonary hypertension, other than isolated CABG, surgery on the thoracic aorta, and
postinfarction septal rupture were not considered due to the nature of the study.
Chronic pulmonary disease and neurological dysfunction were not defined according to
EuroSCORE, and there is no information on patients with unstable angina.

In the real world, with more than 1500 patients, we showed lower mortality among
patients who underwent off-pump CABG^[10]^. So, after a certain cut-off EuroSCORE > 4.5 or 2000
Bernstein-Parsonnet score >17.75, off-pump CABG significantly reduces death
rates. Indeed, numerous large retrospective studies and meta-analyses have shown
significant short-term improvements after OPCAB and comparable long-term outcomes. A
recent risk-adjusted analysis of the national Society of Thoracic Surgeons (STS)
database assessing 876,081 patients demonstrated a significant reduction in death
and stroke (11% and 34% reduction, respectively) after OPCAB, seen in both low- and
high-volume centers^[11]^. After
that, it is important to reconsider the best approach for patients with higher
surgical risk for CABG.

Clearly, a base is being built with strong scientific evidence that this is the group
that experiences the most benefit from off-pump CABG. This evidence allows not using
cardiopulmonary bypass to be the main surgical approach, and complete
revascularization and greater use of arterial grafts in patients with high surgical
risk as the second plan^[12]^.

Actually, randomized controlled trials (RCTs) have failed to demonstrate a
significant mortality benefit for OPCAB^[13]^. However, the available RCTs were underpowered to detect
significant differences between the groups and suffered from high selection and
exclusion biases. Even more important is the fact that the available RCTs so far
have primarily focused only on low-risk (ROOBY, CORONARY), elevated-risk (GOPCABE)
or highrisk patients (BBS), but not on frail patients in whom the benefits of OPCAB
should be well defined. Moreover, the conversion rates (12.4% in ROOBY, 7.9% in
CORONARY, and 5% in GOPCABE) may suggest that some of the participating surgeons
were inexperienced because expert centers report conversion rates between 2% and
4%^[14]^, which
significantly affects long-term outcomes.

We believe that avoiding cardiopulmonary bypass should be viewed primarily as a step
toward avoiding aortic manipulation. Despite the long-term benefits of surgery, some
patients may choose percutaneous coronary intervention (PCI) for the treatment of
complex multivessel disease to avoid the morbidity associated with CABG, of which
stroke is the most feared. Expert OPCAB surgeons can offer equivalent durability of
graft patency as in CABG, with a lower rate of stroke if aortic manipulation is
avoided.

Authors make mistakes in pointing out that on-pump CABG should be able to be
performed under all circumstances, on all patients, at all institutions, regardless
of their cardiac volume^[14]^. Thus,
for example, owing to this rather conflicting evidence, either PCI or CABG surgery
could be offered to patients with chronic kidney disease, depending on the
complexity of coronary disease and comorbidities. If PCI is recommended, appropriate
measures should be employed to prevent contrast-induced worsening of renal function.
If CABG surgery is the preferred revascularization strategy, the off-pump technique
might reduce the risk of acute kidney injury^[15]^.

On the other hand, cardiac scores, including EuroSCORE and STS, have been developed
to predict the risk of adverse outcomes following surgery. Frailty, an independent
predictor of mortality and complications, is not included in these risk algorithms.
Emerging evidence suggests that frailty is a better marker of biological age and
more important than chronological age^[16,17]^. Afilalo et
al.^[18]^ determined that
patients with slow preoperative gait speed (≥6 s to walk 5 m) had a 2 to 3
fold increased risk of mortality and major morbidity for any given level of
STS-Predicted Risk of Mortality or Major Morbidity (PROM) compared with normal
speed. Gait speed added to STS-PROM marginally increased model performance from 0.70
(0.60-0.80) to 0.74 (0.64-0.84). Forty-three percent of patients died or sustained a
major complication assessed as high STS-PROM risk (≥15%) together with slow
gait speed, compared with 21.7% low STS risk with slow gait and 18.9% high STS risk
with normal gait. Afilalo et al.^[19]^ subsequently evaluated the prognostic value of various
frailty, disability and cardiac risk scores to identify the optimal combination to
predict adverse outcome. Patients with slow gait speed and ≥3 impairments on
the Nagi disability scale predicted in-hospital morbidity and mortality above that
of the Parsonnet cardiac risk score (AUC 0.76 *vs.* 0.72 with
Parsonnet score alone). Lee et al.^[20]^ performed a retrospective review of a large cardiac registry,
comparing outcomes between non-frail and frail individuals (coded as having
deficiencies in the activities of daily living, need for walking aids or diagnosis
of dementia). Frailty was an independent risk factor for in-hospital mortality
(risk-adjusted odds ratio [OR] 1.8; 95% confidence interval [CI] 1.1-3.0;
*P*=0.03) and mortality at 2 years (risk-adjusted hazards ratio
[HR] 1.5, 95% CI 1.1-2.2; *P*=0.01).The benefits of CABG without
cardiopulmonary bypass in pre-frail and frail patients are still undetermined.

In conclusion, frailty is defined as a geriatric syndrome of impaired resiliency to
stressors (such as cardiac surgery) that has been delineated recently in the
cardiovascular literature. However, the benefits of CABG without cardiopulmonary
bypass in these patients are still undetermined. We believe OPCAB remains an
important technique for the improvement of coronary surgery. The biggest question
right now is whether pre-frail and frail patients will benefit more from off-pump or
on-pump CABG.

The aim of this paper was to describe the FRAGILE trial protocol which intends to
clarify the potential benefit of off-pump CABG in pre-frail and frail patients; we
will conduct a national multicenter RCT comparing off-pump *versus*
on-pump CABG in frail patients.

## METHODS

### Study Design

The FRAGILE study will be a national multicenter RCT to be conducted in 10
Brazilian institutions. The study is already approved by a certified ethics
committee. The study sponsor must be the Brazilian Society of Cardiovascular
Surgery and Zerbini Foundation. Funding will be provided by an unrestricted
grant from São Paulo Research Foundation, which otherwise will not have
any role in the conduct of the study nor in the analysis nor in the reporting of
data. There will be confidentiality agreement regarding data use. This RCT will
be monitored by an independent data and safety monitoring board. All the authors
will be provided revisions and comments. All the authors will be testifying for
the accuracy and completeness of the report, as well as for the fidelity of the
report to the study protocol.

### Study Population

The inclusion criteria will be: participants aged ≥65 years with
indication of myocardial revascularization with ≥2 criteria of frailty by
Fried Frailty Criteria^[16]^,
not eligible for angioplasty treatment by the heart team approach and those
suitable to undergo either off-pump or on-pump CABG.

There is a dose-response relationship, in relation to the number of fragility
criteria and patient outcomes. The categorization of the fragility variable was
performed after the studies showed that the risk increases gradually over 3
categories (0-1, 2-3, 4-5), with risk of similar events within each category.
Thus, patients who had 2 or 3 criteria were considered as pre-frail, and
patients with 4 or 5 criteria were considered as frail^[21]^.

The exclusion criteria will be: patients with indication of another procedure in
addition to CABG; patients who underwent emergency operation (within 24 hours
after hospital admission); patients who underwent previous cardiac surgery, even
with other approaches than median sternotomy; patients who do not have free,
prior and informed consent to participate in this study.

The baseline characteristics of potentially eligible but excluded patients will
be recorded in a screening log. All patients will be provided written informed
consent.

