### Statistical Analysis

The sample size of the FRAGILE trial was based on the ability to detect a 40%
reduction in the primary outcome in the off-pump group compared with the on-pump
group, assuming an event proportion after on-pump CABG of 20.8% and accepting a
risk of type I and II error of 5% and 20%, respectively, and a crossover rate of
5%^[24]^. Consequently,
at least 630 patients will be enrolled.

All of the data will be analyzed according to intention-to-treat
(*i.e.*, based on treatment allocation). Therefore, we will
report treatment-received analyses according to the intervention actually
received. Baseline characteristics and operative characteristics will be
compared with the use of chi-square test, t-test, or Kruskal-Wallis test, as
appropriate. Dichotomous data will be presented as numbers and percentages.
Continuous data will be presented as mean and standard deviation or median and
interquartile range. The continuity corrected chi-square test will be used for
comparison of the 30-day endpoint. Mantel-Haenszel chi-square tests will be used
to adjust for study-center effects. Treatment effects at 30 days will be
expressed as OR and 95% CI. For the 12-month endpoint, Kaplan-Meier curves will
be constructed, and the study groups will be compared with use of the log-rank
test. HR and 95% CI derived from the Cox proportional hazards model will be
provided for the composite outcome and individual components. All statistical
analyses will be performed with the use of the R-3.1.2 language for handling and
storage of data and performing of statistical calculations.

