the GOPCABE study did not show a significant difference in survival or major adverse
events at 1 year after surgery. This absence of difference may be a consequence of
the requirement for substantially greater experience with off-pump CABG in the
GOPCABE trial than in the ROOBY trial.

With the growth of minimally invasive and transcatheter cardiac interventions, the
expansion of risk prediction beyond traditional risk factors and risk scores has
become a high priority. Clinicians may use this integrative approach of combining
risk scores including frailty and disability to better characterize elderly patients
referred for cardiac interventions and identify those who are vulnerable and at
increased risk. A multidisciplinary team involving cardiac surgery, cardiology,
geriatric medicine, physiotherapy, and occupational therapy may be well suited to
address these diverse elements which contribute to postoperative risk^[19]^.

The CORONARY trial falls short of delivering a knockout victory for the off-pump
technique. There were no significant differences in the rate of the composite
primary outcome of death, stroke, non-fatal myocardial infarction or new renal
failure at 30 days between off-pump and on-pump CABG. However, off-pump CABG was
associated with fewer transfusions, reoperations for bleeding, acute kidney injury,
and respiratory infections or failure. Thus, the off-pump technique may be best in
certain subgroups of patients and we must choose the procedure that is best for
them^[29]^. We hypothesized
that the frailty status would contribute to the risk in patients undergoing on-pump
CABG and that off-pump CABG could be advantageous for frail patients.

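### The primary 30-day analysis adjusts for centre only, although frailty category is known at entry and said to predict outcome; adding it is a small, free improvement to a valid analysis

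*Protocol article*

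**What the plan says.** All references are to the protocol article.

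- **Study Population.** Entry requires at least two Fried criteria. The article states "There is a dose-response relationship, in relation to the number of fragility" criteria and patient outcomes. It reports risk rising over the groups 0-1, 2-3 and 4-5, with similar risk inside each group, and labels 2-3 pre-frail and 4-5 frail. The trial therefore enrols the upper two of three risk groups.
- **Randomization and Treatment.** Allocation is in blocks of ten, stratified by centre only, after baseline data have been entered in the central database.
- **Statistical Analysis.** "The continuity corrected chi-square test will be used for" the 30-day endpoint. Mantel-Haenszel tests adjust for centre, and the effect is given as an odds ratio with 95% CI. No frailty term is named.
- **Sample size (same section).** The trial size is "based on the ability to detect a 40"% reduction, "assuming an event proportion after on-pump CABG of 20.8"%, with "risk of type I and II error of 5% and 20%, respectively, and a crossover rate of" 5%; "at least 630 patients will be enrolled".
- **Discussion.** The authors hypothesize "that the frailty status would contribute to the risk in patients undergoing on-pump" CABG, and that off-pump surgery could help frail patients.

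**The concern.** By the article's own account, the enrolled population mixes two levels of risk, and the variable separating them is fixed before allocation. It is the variable the trial is built around, yet it enters neither the randomization strata nor the stated primary adjustment. This is a criticism of an analysis the article fixes, not of detail left to an unseen plan.

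Two things are at stake, both small. Omitting a prognostic baseline factor from a logistic or stratified analysis costs some power. And if one arm happens to receive more patients with 4-5 criteria, the unadjusted estimate carries that imbalance, whereas an adjusted one largely removes it.

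**Working it through.** **1. The plan's own figure.** On-pump risk 20.8%; a 40% reduction gives 0.6 × 20.8% = 12.48%, a difference of 8.32 points and an odds ratio of 0.543. The mean risk is 16.64%. With two-sided 5% (assumed; sidedness is not stated), 80% power and no continuity correction:

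n per arm = [1.96√(2 × 0.1664 × 0.8336) + 0.8416√(0.208 × 0.792 + 0.1248 × 0.8752)]² / 0.0832² = 313.4, rounded up to 314, so 628 in total.

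This matches 630, so I use 315 per arm. (The match leaves out the 5% crossover and the continuity correction; that is a separate point.)

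**2. Assumed inputs.** The article gives neither the share with 4-5 criteria nor an odds ratio between 4-5 and 2-3. I take a frail share f of 20%, 30% and 50%, and an odds ratio of 1.5, 1.8 and 3.0. The 1.8 (95% CI 1.1-3.0) in the Introduction compares frail with non-frail patients for in-hospital mortality, so it only guides the range. Category risks are set so that the overall risks stay at 20.8% and 12.48%.

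**3. Power with and without frailty category** (Wald test on the log odds ratio).

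Unadjusted: SE = √[1/(315 × 0.208 × 0.792) + 1/(315 × 0.1248 × 0.8752)] = 0.220. Power = Φ(0.611/0.220 − 1.96) = 79.3%.

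Adjusted: within each category, v = the sum over arms of 1/(n p(1−p)); the pooled variance is 1/(1/v_pre + 1/v_frail). Example with f = 30% and odds ratio 1.8:

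- On-pump risks are 17.7% (pre-frail) and 28.0% (frail). The conditional treatment odds ratio is 0.539, giving off-pump risks of 10.4% and 17.3%.
- Patients per arm: 220.5 pre-frail and 94.5 frail.
- v_pre = 0.0311 + 0.0487 = 0.0798; v_frail = 0.0525 + 0.0739 = 0.1264.
- Pooled SE = √0.0489 = 0.221. Power = Φ(0.618/0.221 − 1.96) = 79.8%.

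| Frail share | Odds ratio | Conditional treatment OR | Power adjusted | Gain over 79.3% (points) |
|---|---|---|---|---|
| 20% | 1.5 | 0.542 | 79.5% | 0.2 |
| 20% | 3.0 | 0.530 | 80.7% | 1.4 |
| 30% | 1.8 | 0.539 | 79.8% | 0.5 |
| 30% | 3.0 | 0.529 | 80.9% | 1.6 |
| 50% | 1.5 | 0.541 | 79.5% | 0.2 |
| 50% | 3.0 | 0.530 | 80.8% | 1.5 |

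**4. Chance imbalance.** The SD of the between-arm difference in frail share is about √(2f(1−f)/315). The shift in the risk difference is the imbalance times the on-pump risk gap between categories. With f = 40%, the SD is 3.9 points and 2 SD is 7.8 points.

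- Odds ratio 2 (16.1% vs 27.8%): 0.078 × 0.117 = 0.9 points.
- Odds ratio 3 (13.5% vs 31.8%): 0.078 × 0.184 = 1.4 points.

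That is 11% to 17% of the planned 8.3 points. The SE of the risk difference is √[(0.208 × 0.792 + 0.1248 × 0.8752)/315] = 2.95 points, so the shift is 0.3 to 0.5 SE. At the mild end (f = 20%, odds ratio 1.5) it is 0.064 × 0.071 = 0.45 points, about 0.15 SE.

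**5. Power for an interaction.** The variance of the log ratio of odds ratios is v_pre + v_frail. In the example it is 0.206, SE 0.454. Over the range in step 2 the SE is 0.45 to 0.51. Power is 27% to 34% for a ratio of 0.5, and 22% to 28% for a ratio as large as the planned main effect (0.543). The ratio detectable with 80% power is about 0.24 to 0.29.

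**The case against.** The strongest defence is that nothing is broken. Under randomization the unadjusted test is valid, and its standard error already allows for random imbalance. A 2-SD imbalance occurs in about 1 trial in 20 and even then moves the estimate by at most about half a standard error. The power gain is under 2 points and rests on inputs the article does not supply. All of this stands, and it sets the size of the point. It does not remove it: the article names its adjustment, and a better one is available from data already recorded.

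A reader might be tempted further, in four ways that the document does not support.

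- **That the primary result would be biased.** Chance imbalance is not bias in expectation.
- **That adjustment would add 3 to 5 points of power.** Simulation at 40% frail and odds ratios of 2 to 3 gave 77-78% for the planned test, 80-82% for Mantel-Haenszel by centre and 80-83% by centre and frailty. Nearly all of the difference comes from dropping the continuity correction and adjusting for centre, not from frailty.
- **That frailty is the strongest known predictor.** The article does not say so.
- **That the Discussion's hypothesis requires an interaction test whose absence is an error.** A prognostic gradient does not imply that the treatment effect differs by category. The article often uses frail loosely for the whole enrolled group, and the abstract's Discussion and the Introduction put the question for pre-frail and frail patients together. Subgroup analyses are also commonly left to a full protocol or analysis plan, which is not shown.

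**Conclusion.** The point holds as a minor, cost-free improvement. The stated primary analysis is valid but omits a baseline factor that the article itself calls prognostic and that every patient has on record. Using it would gain roughly 0.2 to 1.6 points of power at 630 patients and guard against an imbalance that, at 2 SD, would shift the risk difference by about 0.5 to 1.4 points. These figures rest on assumed frail shares and between-category odds ratios; if the true odds ratio is near the low end, the gain is negligible.

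It would also be wrong to make the overall conclusion conditional on the pre-frail and frail estimates agreeing. Agreement would need a definition, and with interaction power of about 22% to 34%, the two estimates will often differ by chance.

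**What to change.** In the Statistical Analysis section, name one primary 30-day analysis adjusted for centre and frailty category (2-3 vs 4-5 criteria): either Mantel-Haenszel stratified by centre × category, or logistic regression with both terms, reporting the adjusted odds ratio and 95% CI. Say that this odds ratio is conditional; under the assumptions above it is 0.529 to 0.542, against 0.543 unadjusted, so the shift is small. The unadjusted comparison can stay as a supporting analysis.

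Optionally, list as exploratory the effect in each category with 95% CI and one treatment-by-category interaction, noting the low power. Keep the main conclusion on pre-frail and frail patients combined, whatever the exploratory results show.

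The cost is wording only: no new data, no change to sample size or randomization. It should be fixed before outcome data are seen by arm.
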